### Randomization and allocation concealment

One hundred forty-four eligible participants who have affirmed and signed informed consent will be randomly assigned in a ratio of 1:1:1:1 into the electroacupuncture (EA) + NGF group, the EA + placebo group, the acupuncture + NGF group or the acupuncture + placebo group, each with 36 participants, via a central randomization system, which is managed by a third-party mathematician outside the study and used to generate and conceal the allocation sequence. The randomization sequence will be generated in varying block sizes.

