### Participants

#### Inclusion criteria

Participants will be eligible if they:

(1) Have a first-ever ischemic stroke confirmed by Computed Tomography (CT) and/or Magnetic Resonance Imaging (MRI); (2) have an onset time ranging from 31 days to 90 days; (3) are aged 18 to 80 years, male or female; (4) have dysphagia confirmed by video fluoroscopic swallowing study (VFSS); (5) are able to accept and comply with acupuncture, EA treatment, gluteal intramuscular injection; (6) have already signed consent and exhibit willingness to participate in the trial.

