### Outcomes

#### Primary outcome

The primary outcome is the Functional Oral Intake Scale (FOIS) (20), which reflects the overall intake capability based on swallowing function. The FOIS is a 7-point ordinal scale with a score range of 1–7. Oral intake ability is measured in terms of intake method and food type. Higher scores indicate better oral intake ability. Assessment time frames: at baseline; at week 2, 4, 6, and 12. Week 6 post-intervention is the primary endpoint.

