### Statistical analysis

The overall dropout rate and the dropout rate due to adverse events will be calculated for each group. It will be statistically determined whether each group received the treatment as specified in the study protocol in terms of duration and number of sessions, and the number and percentage of subjects with compliance < 80% will be calculated. Efficacy analysis will be performed in the full analysis set. Participants who have been randomized and have received at least one treatment session will be included in the full analysis set (FAS). All hypothesis tests will be two-sided, and *p*-value < 0.05 will be considered to indicate statistical significance of the tested difference. For ordinal outcomes (FOIS, DOSS, PAS, and mRS), non-parametric tests (Kruskal–Wallis *H* test for group comparisons, with post-hoc Mann–Whitney *U* tests and alpha adjustment) will be used for cross-sectional analyses. For longitudinal ordinal outcomes, generalized estimating equations (GEE) with an appropriate link function (e.g., logit) and working correlation matrix will be the primary method for analyzing these outcomes across multiple time points (FOIS, mRS). The normality of continuous data (MBI, fNIRS metrics) will be assessed using the Shapiro–Wilk test. Provided that parametric assumptions are met, (repeated-measures) ANOVA will be applied. Should the assumptions be violated, non-parametric alternatives (e.g., Kruskal–Wallis test, Friedman test) will be used. The study results will include three-factor (EA factor/NGF factor/time factor) repeated-measure data, with measurement data analyzed using three-factor repeated-measures analysis of variance and ordinal data analyzed using the generalized estimating equation (GEE) to test for differences. The Bonferroni method will be used to adjust for the significance of multiple comparisons.

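### Entry is open from day 31 to day 90 after stroke, yet the stated week-6 analyses make no use of time since onset: a modest loss of precision that is cheap to avoid

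*Protocol article*

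**What the plan says.** All references are to the Protocol article.

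- Inclusion criteria: participants must "have an onset time ranging from 31 days to 90 days".
- Randomization and allocation concealment: participants "will be randomly assigned in a ratio of 1:1:1:1", 36 per arm. "The randomization sequence will be generated in varying block sizes". No stratification factor is named.
- Primary outcome: "The FOIS is a 7-point ordinal scale with a score range of 1–7". It is assessed at baseline and at weeks 2, 4, 6 and 12. "Week 6 post-intervention is the primary endpoint".
- Statistical analysis, cross-sectional comparisons: the rule opens "For ordinal outcomes (FOIS, DOSS, PAS, and mRS), non-parametric tests (Kruskal–Wallis" and continues with post-hoc Mann–Whitney tests at an adjusted alpha.
- Statistical analysis, longitudinal comparisons: GEE "will be the primary method for analyzing these outcomes across multiple time points (FOIS, mRS"). The repeated-measures data are described by three factors (EA, NGF and time), with "ordinal data analyzed using the generalized estimating equation (GEE) to test for differences". Time here is the measurement visit.

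Days since stroke appear only as an eligibility limit. They are not named as a stratum, a covariate or a subgroup.

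**The concern.** The latest eligible entrant is almost three times as far from stroke as the earliest. The six treatment weeks therefore cover different stretches of the post-stroke course, with swallowing training given in every arm. Two participants with the same baseline FOIS, one at day 31 and one at day 90, may have different expected change whatever their allocation. If so, that variation stays in the error of the week-6 comparison, and arms of 36 can differ in mean onset day by chance.

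What is at stake is precision. It matters most for the EA×NGF interaction, which the Introduction makes a central aim. As a difference of differences with n per arm, its standard error is SD·√(4/n). The standard error of a main effect (2n against 2n) is SD·√(2/2n), which is half of that. Onset day must already be recorded to establish eligibility, so leaving it out saves nothing.

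**Working it through.** **1. When the endpoint is read.** If treatment starts at entry, week 6 is entry + 42 days: 31 + 42 = day 73 and 90 + 42 = day 132. The ratio at entry is 90/31 = 2.9.

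**2. What each stated analysis can absorb.** Kruskal–Wallis and Mann–Whitney tests take no covariate. The named factors of the GEE are EA, NGF and visit. Neither uses onset day.

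**3. The plan's own figure.** Sample size: 30 × 1.2 = 36 per arm and 4 × 36 = 144, as stated. No effect size, SD or power is given, so there is no power figure to reproduce. Step 5 sets a benchmark instead.

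**4. Chance imbalance.** Assume entry is spread evenly over the 59-day span.
- SD of onset day = 59/√12 = 17.0 days.
- SE of the difference between two arms of 36 = 17.0 × √(2/36) = 4.0 days.
- Exceeded in 5% of comparisons: 1.96 × 4.0 = about 7.9 days, or 7.9/17.0 = 0.46 SD of onset.
- Carried through to the outcome, the shift is 0.46 × r: 0.05 residual SD at r = 0.1 and 0.18 at r = 0.4.

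**5. Precision.** Let r be the correlation of onset day with week-6 FOIS given baseline. The article gives no value, so a range is shown. FOIS is treated as roughly continuous, and adjustment multiplies residual variance by 1 − r². Benchmark: 30 evaluable per arm (the plan's minimum), two-sided 0.05, and an effect with 80% unadjusted power, (1.960 + 0.842) × √(2/30) = 0.72 SD.

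| r | Variance removed (r²) | Worth, per arm: 30/(1 − r²) | Power after adjustment |
|---|---|---|---|
| 0.1 | 1% | 30.3 | 80.4% |
| 0.2 | 4% | 31.2 | 81.6% |
| 0.3 | 9% | 33.0 | 83.6% |
| 0.4 | 16% | 35.7 | 86.4% |

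At a Bonferroni level of 0.05/6 = 0.0083 (assuming all six pairs of arms are compared), with the effect reset to 80% unadjusted power, the four values are 80.5%, 81.9%, 84.4% and 87.7%.

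**6. Which model term does the work.** Let x be onset day.
- Baseline kept as a visit, main effect γx only: in a linear model, γx enters both week 6 and baseline and cancels from the change. The treatment-by-visit contrast gains nothing.
- Baseline kept as a visit, onset-by-visit term: the change carries (γ₆ − γ₀)x, so differences in rate of recovery are adjusted.
- Post-baseline visits only, baseline FOIS as covariate: γx acts on the later score given the starting score, which is the adjustment wanted.

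**The case against.** The strongest reply is that this is an omission in a condensed article. Covariates are commonly left to an analysis plan, the link and working correlation are left open, and nothing says that covariates are excluded. Part of this stands: a document not shown could add the covariate or a stratum. But the section is not silent. It names the tests, the primary longitudinal method and the model factors, and the rank tests it chooses cannot be adjusted later by adding a term.

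Three further objections stand and limit the point.

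- The article contains no recovery curve and no prognostic figure for onset day, and entry already excludes the first 30 days. A reader might infer that natural recovery differs widely across the window. That is plausible, but the document does not show it.
- The 1 − r² factor belongs to a linear model. With a logit link, a prognostic covariate changes the odds ratio being estimated and need not shrink its standard error. A reader might scale the whole trial, 144/(1 − r²), to 150–171 participants for r = 0.2 to 0.4. Those figures do not describe the proposed FOIS or mRS analysis.
- Chance imbalance is already covered by the type I error and the confidence interval. A reader might infer that stage of recovery confounds the arm comparison. Allocation is randomised, so there is no systematic bias.

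**Conclusion.** The point holds as a modest precision issue. No stated design or analysis feature uses time since onset, although the primary endpoint is read across a 59-day range of time after stroke. For assumed r of 0.1 to 0.4 given baseline, the avoidable residual variance is about 1–16% on a linear approximation. That is worth 0.4 to 6.4 points of power at the benchmark, and under 4 points up to r = 0.3. These figures rest on the assumed r, on treating FOIS as continuous and on 30 evaluable per arm; the imbalance figures also assume evenly spread entry. The documents support neither a claim of bias nor a claim that the loss is large. The change is worth making because it is nearly free, provided it is put where it can act.

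**What to change.** In the Statistical analysis section:

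- Take the week-6 FOIS tests of EA, NGF and EA×NGF from the ordinal model (GEE fitted to the post-baseline visits), not from the Kruskal–Wallis and Mann–Whitney tests.
- Prespecify two covariates in that model: baseline FOIS, and days from stroke onset to randomisation as a continuous variable.
- If baseline is kept as a GEE visit, add an onset-by-visit term. A main effect alone cannot adjust change from baseline.
- Do the same for mRS and for the MBI model, each with its own baseline value.
- Report the distribution of days since onset by arm.

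Cost: a few model degrees of freedom. With a logit link the odds ratio becomes conditional on the covariates, and the plan should say so. No new data or patients are needed. The covariates should be fixed before unblinding, so that an imbalance seen later does not prompt a post hoc adjustment.

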#### Exclusion criteria

Participants will be excluded if they:

(1) Had dysphagia before this ischemic stroke onset or dysphagia not caused by ischemic stroke; (2) have severe cognitive impairment; (3) have a history of multiple strokes, craniocerebral surgery, or cerebral space-occupying lesions; (4) have severe cardiac, hepatic, or renal dysfunction, or other abnormal test results that make the patient unsuitable for participation in this study; (5) have severe neurological deficits prior to ischemic stroke, such as visual and auditory impairments, aphasia, agnosia, severe hemiplegia, and other conditions; (6) are women who are lactating, pregnant or planning pregnancy; (7) have a history of needle fainting or with skin infections at the acupuncture sites; (8) are carriers of a cardiac pacemaker; (9) have a known allergy to NGF; (10) are unable to undergo VFSS; (11) have taken medications that may alter cortical excitability within the past 2 months; (12) are currently participating in other clinical trials or have participated in clinical trials that ended within the last 3 months.

### Intervention

To ensure consistency in interventions, qualified acupuncturists with certifications will be selected and trained. Participants in 4 groups will receive EA/acupuncture and NGF/placebo intervention for 6 weeks, three sessions per week, in inpatient wards and outpatient departments. The locations of all acupoints will be based on the World Health Organization (WHO) Standard Acupuncture Locations (17). The following materials will be used: disposable sterile acupuncture needles of two different specifications (0.25 mm × 40 mm, 0.25 mm × 25 mm; Hwato brand; Suzhou Medical Supplies Factory Co. LTD, Suzhou, China); an acupuncture point nerve stimulator (HANS-200A, Nanjing Jisheng, Ltd., China), a specially made relay (cycled power to the electrode for 6 s on and 6 s off), 20 μg mouse nerve growth factor (mNGF) (NO. S20060051, Jinlujie, Hiteck Biopharmaceutical Co., Ltd., Wuhan, China); 5 mL sterile water for injection (NO. H33022534, Ruixin Pharma, Lishui, China); and 10 mL 0.9% sodium chloride injection (NO. H20043271, China Otsuka Pharmaceutical Co., Ltd., China).

Additionally, swallowing training for dysphagia and conventional treatment for ischemic stroke will be allowed, which are included in the Chinese Guidelines for the Clinical Management of Cerebrovascular Diseases (Second Edition) (18).

### EA + NGF group

A 20 μg dose of mNGF will be dissolved in 2 mL of sterile water for intramuscular injection into the gluteus maximus. Thirty minutes after injection, participants will receive EA treatment. The acupoints GV20 and GV26 will be acupunctured (Figure 3). Participants will lie in the supine position and relax. Prior to acupuncture, 75% alcohol pads will be used to sterilize the skin around the acupuncture points. For GV20, an acupuncture needle (0.25 mm × 40 mm) will be inserted transversely toward the central point of the posterior hairline to a depth of 15–20 mm. For GV26, an acupuncture needle (0.25 mm × 25 mm) will be inserted toward the nasal septum to a depth of 5–10 mm. Acupoints will be stimulated manually until participants feel soreness, distension or heaviness (the reaction of “De Qi”). Then, the needles will be stimulated using an acupuncture point nerve stimulator at a frequency of 2/100 Hz and an intensity tolerable to the participant (targeting 3.0 mA) for 40 min. A specially made relay cycles power to the electrodes in a 6-s on/6-s off pattern. The needles at both acupoints will be retained for 40 min. Participants will receive 18 treatment sessions, 3 times per week for 6 weeks.

**Figure 3 fig3:**
[figure not shown]
Location and needling direction diagram of GV20 (Baihui) and GV26 (Shuigou). This image was generated using BioRender software (http://www.biorender.com).

### EA + placebo group

Participants will receive an intramuscular injection of 2 mL of 0.9% sodium chloride into the gluteus maximus. Thirty minutes after injection, participants will receive EA treatment following the same protocol as the EA + NGF group. Participants will receive 18 treatment sessions, 3 times per week for 6 weeks.

### Acupuncture + NGF group

Participants will receive an intramuscular injection of 20 μg mNGF into the gluteus maximus, as in the EA + NGF group. Thirty minutes after injection, participants will receive acupuncture treatment. The treatment protocol will be similar to that of the EA + NGF group, except that the needles will be connected to an acupuncture point nerve stimulator without actual current output. The device will display a frequency of 2/100 Hz and a current strength of 3.0 mA for 40 min, and a specially made relay will cycle in a 6-s on / 6-s off pattern. When switched on, the apparatus produces the same indicator lights and sounds as the active device but delivers no electrical current. The needles at both points will be retained for 40 min. Participants will receive 18 treatment sessions, 3 times per week for 6 weeks.

### Acupuncture + placebo group

Patients will receive an intramuscular injection of 2 mL of 0.9% sodium chloride into the gluteus maximus. Thirty minutes after injection, they will receive acupuncture treatment following the same protocol as the acupuncture + NGF group. The needles at both points will be retained for 40 min. Participants will receive 18 treatment sessions, 3 times per week for 6 weeks.

### Swallowing training

Prior to initiating swallowing training, a qualified rehabilitation therapist conducts a swallowing assessment of the participant. Based on the evaluation results, rehabilitation goals are established, and an individualized swallowing training plan is formulated. The training program is implemented by a qualified rehabilitation therapist according to the severity of dysphagia. Swallowing training includes direct training techniques (compensatory methods, behavioral maneuvers), and indirect training techniques (orofacial sensory-motor training, airway protection maneuvers) (19). The swallowing training will be administered by a qualified rehabilitation therapist for about 30 min per day, 5 days a week, over 6 weeks.

### Outcomes

#### Primary outcome

The primary outcome is the Functional Oral Intake Scale (FOIS) (20), which reflects the overall intake capability based on swallowing function. The FOIS is a 7-point ordinal scale with a score range of 1–7. Oral intake ability is measured in terms of intake method and food type. Higher scores indicate better oral intake ability. Assessment time frames: at baseline; at week 2, 4, 6, and 12. Week 6 post-intervention is the primary endpoint.

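### Baseline FOIS is collected but is a named covariate in no analysis: the rank tests cannot use it, and the GEE at most treats it as a level of time.

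*Protocol article*

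**What the plan says.** Primary outcome section: "The FOIS is a 7-point ordinal scale with a score range of 1–7". The schedule is "Assessment time frames: at baseline; at week 2, 4, 6, and 12", and "Week 6 post-intervention is the primary endpoint".

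Statistical analysis section: for the four ordinal scales (mRS, PAS, DOSS and FOIS) the plan specifies "non-parametric tests (Kruskal–Wallis *H* test for group comparisons, with post-hoc Mann–Whitney *U* tests and alpha adjustment) will be used for cross-sectional analyses".

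The same section makes a GEE the main longitudinal method and names FOIS and mRS for it. It later describes the data as having three factors (EA, NGF and time), with repeated-measures ANOVA for measurement data and GEE for ordinal data. It names no baseline covariate for any outcome and does not say whether the baseline visit is an outcome in the GEE. It also does not say whether the rank test or the GEE decides the week-6 comparison.

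Secondary outcomes section: DOSS and PAS are taken only at baseline and week 6; mRS and MBI at baseline and weeks 2, 4 and 6.

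Randomization section: allocation is 1:1:1:1 with 36 per arm, and "The randomization sequence will be generated in varying block sizes". No stratification factor is mentioned. The inclusion criteria ask for dysphagia confirmed on VFSS, and neither criteria list sets a FOIS limit.

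**The concern.** Oral intake at entry is likely to predict oral intake six weeks later. With 36 per arm, two things follow from leaving it out. Between-patient variation that could be explained stays in the comparison and costs power. Any chance difference in starting severity between arms also passes straight into a week-6-only test.

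Treating baseline as a level of time uses the measurement, but poorly. If a treatment main effect is taken over all visits, one of those visits precedes treatment, and the true difference there is zero by randomisation. If the treatment-by-time contrast from baseline to week 6 is used, the result behaves like a change score, which subtracts the whole baseline rather than the fraction of it that predicts the outcome.

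The trial describes itself as small and wants to separate two factors and their interaction, so the lost information matters.

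**Working it through.** **The plan's own figure.** 30 per arm × 1.2 = 36, and 36 × 4 = 144, which reproduces the stated sample size. The article gives no effect size, SD, correlation or power, so there is no power figure to reproduce. Everything below rests on assumed values: r from 0.3 to 0.7 and, for power, an effect of 0.5 SD at two-sided 0.05 with the stated minimum of 30 per arm.

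**Where baseline FOIS can enter, as written**
- Rank tests at week 6: nowhere.
- GEE, week-6 difference between arms read directly: baseline contributes no adjustment (variance factor 1).
- GEE, treatment-by-time contrast from baseline to week 6: roughly a change score, variance factor 2(1−r).
- GEE, main effect over all visits: baseline dilutes it. On a linear scale, with equal visit weights and a constant effect from week 2, the FOIS main effect is (0+1+1+1+1)/5 = 0.80 of the true effect. For mRS, with four visits, it is (0+1+1+1)/4 = 0.75.

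**Variance under covariate adjustment (linear approximation)**

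Against week 6 alone the factor is 1−r². Against a change score it is (1−r²)/[2(1−r)] = (1+r)/2.

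| r | change score 2(1−r) | adjusted 1−r² | adjusted ÷ change score |
|---|---|---|---|
| 0.3 | 1.4 | 0.91 | 0.65 |
| 0.5 | 1.0 | 0.75 | 0.75 |
| 0.7 | 0.6 | 0.51 | 0.85 |

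Adjustment is the smallest at every r below 1. As sample-size equivalents, the gain over week 6 alone is 1/0.91 = 1.10 to 1/0.51 = 1.96, and over a change score 1/0.65 = 1.54 to 1/0.85 = 1.18. The two gains run in opposite directions as r rises.

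**Power for 0.5 SD, before any Bonferroni correction**

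| Comparison | Week 6 only | Adjusted, r = 0.3 | r = 0.5 | r = 0.7 |
|---|---|---|---|---|
| One arm against another, 30 v 30 | 49% | 53% | 61% | 77% |
| Factorial main effect, 60 v 60 | 78% | 82% | 89% | 97% |

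For the 60 v 60 main effect, the change-score contrast gives 64%, 78% and 94% at the same three values of r. At r = 0.5 or below it is no better than ignoring baseline.

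**Check on a seven-category scale.** A simulation (30 per arm, 0.5 SD latent shift, nobody starting at the top, 3,000 runs per setting) compared a Mann–Whitney test at week 6 with a rank analysis adjusted for baseline. Mann–Whitney power was about 43%. Adjusted power was 46%, 52% and 65% at r = 0.3, 0.5 and 0.7.

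**Check on the logit scale.** In a simulated proportional-odds model (60 v 60, same shift, r = 0.5 to 0.7), adding baseline raised the mean standard error of the log odds ratio from 0.33 to 0.34–0.35. The conditional estimate grew by more than that, so power rose. The variance factors above should therefore not be read as interval widths for a logit model.

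**The case against.** The strongest reply is that baseline is not ignored. It heads the list of FOIS visits, and the plan has a GEE with a time factor, so the natural reading is that baseline is a level of time. That stands, and a reader who infers that baseline FOIS is used nowhere goes further than the text allows. It reduces the gain from adjustment but does not remove it, since 2(1−r) exceeds 1−r² for every r below 1. A longitudinal model that constrains the arms to a common baseline would recover most of the gain, but the article does not describe one.

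A second reply is that covariates belong in an SAP, which is not shown. The article does more than stay silent, however: it selects tests that admit no covariate and lists the factors of the longitudinal model. An SAP could still refine this.

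Other tempting inferences do not hold:
- *Patients at the ceiling will dilute the effect.* The criteria do not exclude someone at or near FOIS 7, who could improve little or not at all. But no baseline distribution is given, and VFSS-confirmed dysphagia may make such patients rare. Any ceiling share would be invented.
- *Randomisation is unstratified.* The article names no stratum, but the full protocol may. Blocked randomisation without severity strata is valid in any case, and chance imbalance is not bias.
- *Every confidence interval is wider without baseline.* Not in a logit model, as the check shows.

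On DOSS and PAS, the closing sentence of the plan sends ordinal repeated data to GEE in general and might cover them. If so, they meet the same level-of-time problem with only two visits.

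**Conclusion.** The point holds as a matter of efficiency and clarity; it is not an error of validity. The stated tests either cannot use baseline FOIS or use it less well than a covariate would, and DOSS and PAS have the same weakness under the rank tests named for them.

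The direction of the loss is certain for any positive correlation below 1. Its size is not known from the document. At r = 0.3 the gain over a week-6-only test is small (four percentage points for either comparison above); at r = 0.7 it is worth nearly a doubling of the sample. These figures rest on an assumed 0.5 SD effect and a linear approximation, which the seven-category simulation supports in direction. The ceiling and stratification questions do not form part of the conclusion.

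**What to change.** - Name one primary analysis of week-6 FOIS: a proportional-odds model, or an ordinal GEE, with EA, NGF, EA×NGF and baseline FOIS as a covariate.
- If the GEE is used, enter only weeks 2, 4, 6 and 12 as outcomes. Include treatment-by-visit terms so that the week-6 effect can be read from the model.
- State in advance how baseline FOIS is coded, and that the resulting odds ratio is conditional on baseline.
- Adjust DOSS, PAS, mRS and MBI for their own baselines. Keep the rank tests, if wanted, as supportive.

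The measurements are already scheduled, so the cost is a change of text, to be made before unblinding. Stratifying the central randomisation by baseline FOIS is optional and would apply only to participants not yet enrolled. No entry limit on FOIS is proposed, because the document gives no basis for one.
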